## **8. Observed indicators and inspection time**

### **8.1 Examinations before entering the groups**

- Physical examination, vital signs and physical status score;
- Blood routine, liver and renal function;
- Hepatitis virus;
- ECG;
- Imaging studies: (B ultrasound must be carried out; enhanced abdominal CT or MRI was needed) In order to reduce the detection error, the method of examination of the tumor lesion hospitals and the equipments for use must be consistent;
- Serum tumor markers: AFP, CEA, and CA199.

### **8.2 Examinations during the study**

- Physical examination, vital signs and behavioral state classification;
- Blood, urine routine;
- Liver and kidney function;
- Imaging studies;
- Tumor markers (such as: AFP, CEA, and CA199).

The above examinations could be carried out every 2 to 3 months in the treatment hospitals or local hospitals.

## **9. Follow-up**

Patients must be arranged for close follow-up which included rechecks every 2-3 months or contact by phone after entering the treatment group.

Follow-up will be carried out according to the following stipulations with CRF filling:

Every 2 to 3 months: blood routine, liver and kidney function, AFP, liver ultrasonography;

Every 3 to 4 months: enhanced abdominal CT or MRI.

Every six months: chest X-ray or chest CT;

If the patient had signs of distant metastases of the lung, bone, intracranial, whole-body bone scan, CT of other parts, and even PET-CT should be added.

## **10 Clinical evaluations: the judgment of efficacy is mainly based on the following indicators**

### **10.1 The main evaluation indicators**

Time to recurrence (TTR): the time between the date of surgery and being found recurrence by examination. In case patients are lost to follow, or with unexplained death, TTR are calculated until this point.

Recurrence: new intrahepatic lesions are found in abdominal CT or MRI with the typical characteristics of enhancement in arterial phase, degradation in portal and delayed phase; chest X-ray finds lung metastasis which should be confirmed by lung CT; If there are any symptoms of adrenal gland, bone, intracranial and other metastasis, abdominal CT, bone scan, and other relative examinations should be used as diagnosis.

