## 4.2 Population and Period

The total number of cases is 68.

It was reported that the median tumor-free survival time or median recurrence time was 13-24 months after a curative surgery for HCC. In this study, the median recurrence time of the control group is supposed to be 18 months. That of the group of patients with implantation of  $^{125}\text{I}$  is expected to be 36 months (the hazard ratio of  $^{125}\text{I}$  was 0.5). A probability value of  $<0.05$  in one-sided test is considered statistically significant. Power of the test was 0.80. The number of cases in the study is 68.

These patients will be treated in our hospital from July 2000 to June 2004. The follow-up period was extended to 5 years after surgery.

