### **10.2 Secondary evaluation indicators**

Overall survival (OS): The time between the administrations of the drugs after entering the groups and death or lost follow up of the study individuals.

1, 3, 5-year survival rate: it refers to the percentage of still living individuals after 1 year, 3 years, five-year.

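### The TTR rule gives loss and unexplained death no event or censoring status, dates them by loss or death rather than last imaging, and omits explained deaths without recurrence

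*Protocol*

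**What the plan says.** Section 10.1 defines TTR as "the time between the date of surgery and being found recurrence by examination". Recurrence in the liver means that "new intrahepatic lesions are found in abdominal CT or MRI with the typical characteristics of enhancement in arterial phase", with the washout pattern that the section goes on to describe. Spread elsewhere is also confirmed by imaging. For patients in whom this does not happen, the section adds: "In case patients are lost to follow, or with unexplained death, TTR are calculated until this point".

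Section 9 asks for "rechecks every 2-3 months or contact by phone after entering the treatment group". It then sets a schedule that includes ultrasonography every 2 to 3 months, chest imaging every six months and "Every 3 to 4 months: enhanced abdominal CT or MRI".

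Section 10.2 words overall survival in a similar way, ending it at "death or lost follow up of the study individuals". Section 13.2 names life tables, Kaplan-Meier, log-rank and Cox regression, and gives no censoring rule.

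**The concern.** The methods in section 13.2 need a time and a status for every patient. For the sole primary endpoint, the sentence in section 10.1 leaves three things unsettled.

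1. **Status.** Loss and unexplained death are treated alike, and neither is called an event or a censored time.
2. **Date.** Time runs to the loss or the death. A recurrence can be seen only on imaging, so the interval between the last scan and that date held no chance of an event, yet it counts as recurrence-free.
3. **Deaths.** Only unexplained deaths are named. A death from a known cause without recurrence has no rule.

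The HR then depends on a choice that could be made after the data are seen. Control patients receive no implant, and the protocol describes neither masking nor independent reading of scans, so missed scans and loss could differ by arm.

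**Working it through.** **Inputs from the protocol.** Section 4.2 states that "the median recurrence time of the control group is supposed to be 18 months". The implant arm has an expected median of 36 months (HR 0.5). The test is one-sided at 0.05 with power 0.80, there are 68 patients, and follow-up is 5 years. No dropout allowance is stated.

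**Assumptions.** Allocation is 1:1 and times are exponential. The documents give no loss rates, so 10%, 20% and 30% by 60 months are used, unrelated to recurrence.

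**Step 1: the plan's own figure.**
- Events (Schoenfeld): 4 × (1.645 + 0.842)² / (ln 0.5)² = 51.5, so 52.
- Hazards per month: ln 2/18 = 0.03851 and ln 2/36 = 0.01925.
- Probability of recurrence by month 60: 1 − exp(−0.03851 × 60) = 0.901 and 1 − exp(−0.01925 × 60) = 0.685. The mean is 0.793.
- N = 52/0.793 = 66. An exponential (Lachin-type) formula gives 70.

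The stated 68 is reproduced to within 2, with recurrences as the events and no dropout. With 68 patients and no loss, 68 × 0.793 = 53.9 events are expected, and one-sided power is 0.82.

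**Step 2: losses counted as events.** The monthly loss rate is g = −ln(1 − q)/60: 0.00176 for q = 10%, 0.00372 for 20% and 0.00595 for 30%. The apparent HR is (λ_implant + g_implant)/(λ_control + g_control).
- Control 30%, implant 10%: (0.01925 + 0.00176)/(0.03851 + 0.00595) = 0.47.
- Control 10%, implant 30%: (0.01925 + 0.00595)/(0.03851 + 0.00176) = 0.63.
- No true effect, the same two cases: (0.03851 + 0.00176)/(0.03851 + 0.00595) = 0.91, and its inverse 1.10.

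**Step 3: unimaged time credited.** A Cox model was fitted to 200,000 simulated patients per arm. Imaging stops at rate g, later recurrences go undetected, and the patient counts as recurrence-free to month 60. This is the extreme form, since it assumes that contact always lasts to month 60.

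**Step 4: censoring at the last imaging.** The same patients are censored when imaging stops.

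| True HR | Loss by 60 months, control / implant | Counted as events | Unimaged time credited | Censored at last imaging |
|---|---|---|---|---|
| 0.50 | 10% / 10% | 0.52 | 0.51 | 0.50 |
| 0.50 | 20% / 20% | 0.54 | 0.53 | 0.50 |
| 0.50 | 30% / 30% | 0.57 | 0.54 | 0.50 |
| 0.50 | 30% / 10% | 0.47 | 0.60 | 0.50 |
| 0.50 | 10% / 30% | 0.63 | 0.45 | 0.50 |
| 1.00 | equal, 10% to 30% | 1.00 | 1.00 | 1.00 |
| 1.00 | 30% / 10% | 0.91 | 1.15 | 1.00 |
| 1.00 | 10% / 30% | 1.10 | 0.87 | 1.00 |

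Values are rounded. Simulated values that should equal 0.50 or 1.00 were within 0.006 of them.

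**Step 5: power with equal loss of 10%, 20% and 30%** (one-sided 0.05, 68 patients, true HR 0.50). Censored at last imaging: 51.9, 49.9 and 47.7 events, with power 0.80, 0.79 and 0.77. Losses counted as events: power 0.78, 0.74 and 0.70.

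**The case against.** The strongest reply is that the sentence is an informal description of censoring. Section 10.1 has already tied TTR to recurrence found by examination, and section 13.2 names methods for censored data. Section 10.2 words overall survival in the same way, where reading loss as death would be absurd. This stands: a reader might infer that dropouts are to be counted as recurrences, but that is the weaker reading. It does not settle the date, and it does not cover explained deaths.

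A reader might also infer that phone calls replace scans. They do not formally do so: section 9 schedules CT or MRI every 3 to 4 months, and section 8.2 lets examinations be done in local hospitals, so a call may simply collect a local result. What remains is that nothing says how TTR is dated when a scan is missed and only a call is made.

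A third inference is that the rule favours the implant. Nothing in the protocol suggests which arm would lose more patients, and the table shows bias both ways. Nor does the rule remove treatment-related deaths from the comparison. Such a death is explained and so falls outside the sentence, and it still counts in overall survival.

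Finally, it may be said that this belongs in a statistical analysis plan. The finer detail of a competing-risk analysis can go there. The rule itself, however, stands in the protocol's definition of its primary endpoint and is incomplete as stated.

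**Conclusion.** The point holds as a badly fixed rule in the primary endpoint: no status, a date not tied to imaging, and no provision for explained deaths without recurrence. It does not show that the trial's result is biased. Under no true effect, bias needs loss that is unequal or informative. If a true effect exists, equal loss handled in either of the two faulty ways only pulls the HR toward 1 (0.51 to 0.57 for a true 0.50).

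With 10% loss in one arm and 30% in the other, a true HR of 0.50 is reported as 0.47 to 0.63 (losses as events) or 0.45 to 0.60 (unimaged time credited). A true HR of 1.00 is reported as 0.91 to 1.10 or 0.87 to 1.15 respectively. The two readings move the HR in opposite directions. These sizes rest on assumed loss rates, exponential times and, for the credited case, contact lasting to month 60. Censoring at the last imaging recovers the true value only if loss is noninformative.

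**What to change.** Replace the sentence in section 10.1 with:

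> Only recurrence documented by imaging as defined here is a TTR event. A patient alive or lost without documented recurrence is censored at the last CT/MRI showing no recurrence; phone contact updates survival status only. Any death without documented recurrence, explained or unexplained, is not a recurrence and is handled by one stated rule in both arms (competing event at the date of death), with a sensitivity analysis counting recurrence or death from any cause as the event.

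The cost is a change of wording, slightly less person-time and one extra supportive analysis. If losses are noninformative, censoring them costs about 1 to 4 points of power at 10% to 30% loss. That follows from the loss itself and not from the new wording.

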### **10.2 Secondary evaluation indicators**

Overall survival (OS): The time between the administrations of the drugs after entering the groups and death or lost follow up of the study individuals.

1, 3, 5-year survival rate: it refers to the percentage of still living individuals after 1 year, 3 years, five-year.

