## 4.3 Grouping

All of the patients will be grouped after receiving curative surgeries for HCC.

$^{125}\text{I}$  treated group: The wound will carefully stanch after the tumor have been removed completely. The square meter of the wound will be measured and the data will be input into the computer to determine the number of radionuclides will implant and doses. Mick radionuclide applicator will be used to implant  $^{125}\text{I}$  at 1cm interval in the normal liver tissues at the incisional margin ( $^{125}\text{I}$  was produced in Reactor Engineering Research of China Institute of Atomic Energy with  $0.8\text{mm} \times 4.5\text{mm}$  and a half-life of 59.6 days and enveloped with Nickel titanium alloy. It is sterilized under high temperature. It has X-ray with energy of 27.4-31.5Kev and  $\gamma$ -ray with energy of 35.5 Kev. The activity of per seed is 0.5-0.6mCi). Ultrasonography is utilized to see whether seeds are well-distributed. More seeds will be implanted so as to avoid cold spot areas if seeds are not well-distributed. Fibrin gel will be smeared on wounds and then sutured with absorbable gelatin sponge or hemostatic gauze to prevent  $^{125}\text{I}$  from dropping off.

Control group: The rest treatment will be the same as that of the  $^{125}\text{I}$  treated group except for implantation of  $^{125}\text{I}$ .

Both of the groups received identical routine support treatment for the liver after surgery.

All of the patients will receive venous blood collection on one day before surgeries and day 7 after surgery. Aminotransferase and bilirubin were measured. AFP and MMP-9 will be measured via radioimmunoassay. Meanwhile, activity of nature killer cells and T cell subsets will be measured by flow cytometers (America COULTER). Curative hepatectomy of HCC must meet these following conditions: a. Tumor is completely removed. Explorations during surgery show no tumor remaining and fast pathology results revealed that there are no cancer cells in the incisional margins. b. There are no macroscopic cancer emboli in the main side branches and bile duct bifurcations. c. The number of the tumor is less than three. d. There is no extrahepatic metastasis.

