### **5.2.2 Interventions of two groups after removal of the tumor**

I group: The wound will be carefully stanch after the tumor has been removed completely. The square meter of the wound will be measured and the data will be input into the computer to determine the number of radionuclides implanted and doses. Mick radionuclide applicator will be used to implant I at 1cm interval in the normal liver tissues at the incisional margin (I was produced in Reactor Engineering Research of China Institute of Atomic Energy with 0.8mm×4.5mm and a half-life of 59.6 days and enveloped with Nickel titanium alloy. It is sterilized under high temperature. It has X-ray with energy of 27.4-31.5Kev and γ-ray with energy of 35.5 Kev. The activity of per seed is 0.5-0.6mCi. The prescription dose was 160Gy). Ultrasonography is utilized to see whether seeds are well-distributed. More seeds will be implanted so as to avoid cold spot areas if seeds are not well-distributed. Fibrin gel will be smeared on wounds and then sutured with absorbable gelatin sponge or hemostatic gauze to prevent I from dropping off. The rest treatment of the control group is the same as that of the I treated group except for implantation of I. Both of the groups will receive identical routine support treatment for the liver after surgeries.

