7.2.2 The procedure of preservation and distribution

Each patient of the group will obtain a random number, and then the number will be reported to the preservers of the center by the researchers. The preservers would judge whether to use seeds which will be distributed to the patients with the corresponding number.

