#### **13.2 Statistical analysis**

Professional statistical workers will undertake statistical analysis tasks, and participated in the whole process from experimental design and implementation to analysis and summarization. After the completion of the trial protocol and CRF, the development of statistical analysis plan is formulated, and the statistical analysis report will be provided after the necessary changes in the analysis during the testing process.

Statistical methods: the statistical quantitative index include mean, standard deviation, median, minimum, maximum. All statistical tests use two-sided test,  $P \leq 0.05$  is considered to have statistically significant difference. The comparison among enumeration data use  $\chi^2$  test. The inter-group comparison of measurement data took use of t test after normal step test and homogeneity test for variance. We use life table for the estimation of survival rate, Log-rank test for the comparison of survival rate among groups and Kaplan-Meier method for survival curves. COX regression analysis will be for the relevant factors affecting patients' survival.

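### The overall survival definition starts at a date control patients do not have and ends at death or loss without saying which is the event

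*Protocol*

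**What the plan says.** Section 10.2 defines OS as "The time between the administrations of the drugs after entering the groups and death or lost follow up of the study individuals". It explains the 1-, 3- and 5-year survival rates thus: "it refers to the percentage of still living individuals after 1 year, 3 years, five-year".

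Section 10.1 starts the primary endpoint elsewhere. TTR is "the time between the date of surgery and being found recurrence by examination", and for patients who are lost or die without explanation the time runs to that point.

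On what controls receive, section 4.3 reads "Control group: The rest treatment will be the same as that of the" seed-treated group, implantation excepted. Section 5.2.2 repeats this: "The rest treatment of the control group is the same as that of the" seed group, again apart from the implant. Both arms then get the same routine liver support. In the seed arm the implant is part of the operation, once the tumour is out: "Mick radionuclide applicator will be used to implant" the seeds at the resection margin. Section 7.2.2 ties seed release to the patient's random number: "The preservers would judge whether to use seeds which will be distributed to the patients with the corresponding number".

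Section 13.2 names the methods. On rates it says "We use life table for the estimation of survival rate"; it adds the log-rank test for comparing groups and Kaplan-Meier for the curves. No section says whether loss to follow-up is an event or a censoring for OS.

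**The concern.** A time-to-event endpoint needs an origin that every patient has and an end that separates events from censorings. The OS sentence supplies neither.

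- **Origin.** If the administration it refers to is the seed implant, no control patient has a start date. Whoever builds the dataset must choose one, and the primary and secondary endpoints then rest on different written origins. A substitute that falls later in controls than in seed patients would treat early postoperative deaths differently by arm.
- **End.** Death and loss share one clause with equal standing. A programmer who follows it literally could code both as events. OS would then be time to death or dropout: survival would be understated, a real effect would be diluted, and a difference in dropout between arms would look like a difference in survival. Follow-up lasts five years, partly at local hospitals or by telephone (sections 8.2 and 9), so some loss is plausible. The protocol describes neither sham nor blinding, so unequal loss is possible.

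**Working it through.** **1. The plan's own figure.** The only related number is the sample size of 68 (section 4.2), built on TTR: medians 18 and 36 months, hazard ratio 0.5, one-sided 0.05, power 0.80. The allocation ratio is not stated; 1:1 is assumed here, with exponential times and 60 months of follow-up.

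- Events (Schoenfeld): 4 × (1.645 + 0.842)² / (ln 0.5)² = 4 × 6.18 / 0.480 = 51.5, so 52.
- Event probability by 60 months: control 1 − 2^(−60/18) = 0.901; seed arm 1 − 2^(−60/36) = 0.685; mean 0.793.
- N = 52 / 0.793 = 65.6, so 66. The unpooled log-hazard form gives 6.18 × (1/0.901 + 1/0.685) / 0.480 = 33.1, so 34 per arm and 68 in total.

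The 68 reproduces. No OS quantity enters it, so the OS definition cannot change it.

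**2. The origin, arm by arm.**

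| | Seed arm | Control arm |
|---|---|---|
| TTR origin (10.1) | date of surgery | date of surgery |
| OS origin (10.2), read as the implant | implant, during surgery | none |
| OS origin (10.2), read as routine liver support | after surgery, day not fixed | after surgery, day not fixed |

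The first OS reading gives controls no origin. The second gives both arms a date, but the protocol does not fix it, and a death before the first dose would have no start. Taking the implant for one arm and supportive treatment for the other would give the arms unequal origins. Surgery is the date that both arms share and that TTR already requires.

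**3. The end.** The clause says where the measured time stops, not what status is recorded there. It also gives no stopping point for a patient alive at the end of follow-up.

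**4. What the literal reading could do.** These inputs are assumptions, not design figures: exponential survival, control 3-year OS of 65%, and constant yearly loss d independent of death.

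- Control death hazard: −ln(0.65)/36 = 0.01197 per month.
- Loss hazard: −ln(1 − d)/12 = 0.00168, 0.00427 or 0.00878 per month for d = 2%, 5% or 10%.
- With losses coded as deaths, the hazards add. Apparent hazard ratio = (HR × 0.01197 + loss hazard in seed arm) / (0.01197 + loss hazard in control).

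| Yearly loss, both arms | Control 5-year survival | Apparent HR if true HR is 0.50 |
|---|---|---|
| 0 | 48.8% | 0.50 |
| 2% | 44.1% | 0.56 |
| 5% | 37.7% | 0.63 |
| 10% | 28.8% | 0.71 |

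With no true effect and unequal loss:

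| Yearly loss, control | Yearly loss, seed arm | Apparent HR |
|---|---|---|
| 10% | 2% | 0.66 |
| 5% | 2% | 0.84 |
| 2% | 5% | 1.19 |

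The bias can go either way. If losses are censored, and loss is independent of death as assumed here, none of these distortions arises.

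**The case against.** The strongest reply is that a competent analyst would not go wrong. The seed arm is treated during the operation, so its administration date is the surgery date; every patient's surgery date is needed for TTR, and surgery is the obvious common origin. The reference to drugs looks like template wording: section 6 also mentions chemotherapy vomiting and HAMA responses, which do not fit a seed implant. The end clause may be a loose way of saying death or last contact. Section 10.1 likewise describes where time stops, the methods in section 13.2 all handle censoring, and censoring rules are commonly left to the statistical analysis plan.

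Much of this stands. A reader might infer that the protocol counts dropouts as deaths; it does not say so, because it assigns no event status. A reader might also infer that section 10.2 defines a crude percentage at odds with section 13.2. That does not follow: section 10.2 says what the rate means, section 13.2 says how it is estimated, and the two are compatible. Nor does section 13.2 direct a chi-square test at survival rates; it assigns the log-rank test to them.

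The reply does not remove the point. This is more than an omission: the protocol states an origin, and that origin cannot be applied to one arm. An analysis plan would have to depart from the written definition to use surgery. Since the protocol also states an end for OS, it should not leave open whether that end is an event.

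**Conclusion.** The OS definition is wrong as written on its origin and ambiguous on its end. The origin fault rests on the text alone and affects every control patient. A reader might put that at half the trial, but the allocation ratio is not stated and the document does not support a count. If surgery is used, as is natural, the practical effect of the origin fault is likely small.

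The end fault would bias the result only if losses were in fact coded as deaths, and the size would then depend on loss rates the protocol does not give. The hazard ratios above show what that reading could do under assumed rates; they do not estimate what will happen in this trial.

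Severity is moderate. OS is a secondary endpoint, the needed date exists for every patient, and neither the primary endpoint nor the sample size is affected.

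**What to change.** Replace the OS definition in section 10.2 with:

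> OS is the time from the date of surgery (the same origin as TTR, in both arms) to death from any cause. Patients alive or lost to follow-up are censored at the date last known alive.

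Add that the 1-, 3- and 5-year rates are read from the life-table or Kaplan-Meier estimate already named in section 13.2.

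The cost is a wording change. It alters no visit and leaves the sample size at 68. The one data item to confirm is that the case report form records the date each patient was last known alive.
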